### Eligibility and participant recruitment

2.5

Participants entering REFINE will be patients with locally advanced or metastatic cancer receiving ICI as SOC and responding to treatment (complete/partial response or stable disease radiologically) at 12 weeks in the UK. They must satisfy the eligibility criteria summarised in Table 1 and 2. Randomisation can occur anytime up to 6 weeks after the last dose of the first 12 weeks of treatment.

### Site recruitment

2.6

REFINE is open to NHS hospitals throughout the United Kingdom (UK). Site recruitment has been organised in ‘waves’ of hospitals, grouped by their accrual to RAMPART (a phase III trial platform trial of adjuvant therapy in high/intermediate risk RCC) and PRISM (a randomised phase II trial of nivolumab with alternatively scheduled ipilimu-mab in advanced/metastatic RCC) [22,23]. This has enabled more individualised site support and enabled the optimisation of training and materials provided to hospital sites. Information for sites is regularly updated on the trial website: http://refine.mrcctu.ucl.ac.uk/. All participating sites will be managed by the MRC CTU at UCL.

### Randomisation

2.7

REFINE will randomise participants centrally through an interactive web-based system using minimisation (with a random element) with stratification by a small number of important stratification factors. For stage I, patients will be randomly assigned in the ratio 1:1 to Arm A (SOC interval) and Arm B (extended interval). The precise allocation ratio for stage II will be determined after completion of stage I, but it is anticipated that more patients will be allocated to the added arms than to the existing stage I arms, to achieve approximately equal total allocation between all arms.

### Co-enrolment

2.8

Participants previously enrolled in interventional trials may be eligible for recruitment to REFINE, if they have not received prior ICI. REFINE participants should not join any other interventional trial during treatment in REFINE, unless they have experienced disease progression. Co-enrolment in non-interventional studies is permitted if it does not interfere with the REFINE treatment/assessment schedule.

### Treatment schedule and assessments

2.9

Participants in Arm A will receive SOC interval ICI (480 mg nivo-lumab 4 weekly after ipilimumab and nivolumab regimens) commencing 6 weeks after their last infusion prior to randomisation.

Participants in Arm B will receive extended interval ICI, which in stage I is doubling the dosing interval of Arm A (SOC interval):

Additional tumour cohorts will mirror the renal cohort if treated with ipilimumab/nivolumab combinations (e.g. patients with melanoma) randomised at the point they proceed to nivolumab monotherapy. If treated with pembrolizumab (e.g. melanoma or mismatch repair-deficient Colorectal Cancer) with a SOC of 400 mg pem-brolizumab 6 weekly, the experimental arm for stage I will be 12 weekly administration.

Treatment will be given as part of the trial until disease progression, toxicity that precludes further treatment, participant preference or for 1 year 9 months from the start of randomised treatment (i.e. 2 years total treatment). Participants who are still responding to ICI treatment at 2 years will have the option to continue treatment off trial if part of their normal care. Participants experiencing progression on the extended dosing interval (Arm B) will be offered treatment intensification (i.e. reverting to SOC ICI dosing frequency, as per Arm A) at the participants and clinician's discretion.

The trial assessment schedule for each cohort is aligned with standard practice. Participants will be clinically assessed at baseline and every 4 weeks for the trial duration regardless of treatment status or progression. Since the COVID-19 pandemic clinical assessments are often conducted remotely, and the REFINE assessment schedule supports this, if possible, to collect all necessary clinical information and this is deemed appropriate by the investigator.

Participants in both arms have a CT with contrast of the chest, abdomen and pelvis (or Positron Emission Tomography (PET)-CT +/− brain surveillance if appropriate in the melanoma cohort) carried out at baseline and then every 12 weeks until disease progression or treatment discontinuation, whichever occurs later.

### Treatment beyond progression

2.10

Participants will be permitted to continue treatment beyond initial progression if they meet the following criteria:

Investigator-assessed clinical benefitTolerance of study drugStable performance status

Participants on Arm B (extended interval ICI) who experience progression and are clinically fit to continue treatment may continue the extended interval dosing or will have the option to intensify their treatment (i.e., cross over back to Arm A regimen). ICI treatment should be discontinued permanently upon documentation of further progression.

### Criteria for discontinuing allocated interventions

2.11

An individual participant may stop treatment early for any of the following reasons:

Disease progressionUnacceptable toxicity, intercurrent illness or change in patient's condition that justifies discontinuationInadequate compliance with the protocol treatment, in the judgement of the treating physicianPregnancy or intent to become pregnantGrade ≥ 3 infusion reactionInitiation of alternative anticancer therapy including another investigational agentAny dosing interruption lasting >6 weeks although dosing delays or interruptions to allow for prolonged steroid tapers to manage drug-related adverse events are allowed.Withdrawal of consent for treatment by the patient

### Participant follow up

2.12

Participants will be followed up for 1 year and 9 months from randomisation, regardless of treatment status or progression. Longer term data including information on progression and survival will be collected on an annual basis until the end of the trial.

### Tumour assessment

2.13

PFS outcome will be investigator-reported and will be based on radiological progression according to RECIST 1.1 criteria. Radiology reports will be collected and reports on progression will be reviewed blinded to treatment allocation.

### Safety/toxicity management

2.14

ICI stimulate a host immune response against tumour cells. They can also lead to activation of self-reactive T cells that can damage healthy tissue and result in immune related adverse events (ir-AEs) which can affect any body system. A current list of ir-AEs is available to investigators in the Reference Safety Information (RSI). ir-AEs should be managed as per local and national/international guidelines.

### Duration

2.15

It is expected that recruitment to stage I will complete in approximately 12 months. Analysis of disease control will be performed at approximately 6 months from completion of stage I recruitment. As the results of stage I will inform which arms are included in stage II, during this time randomisations will be paused. It is then expected that recruitment to stage II will complete in a further 12 months. Analysis of disease control will be performed within 12 months of recruitment completion.

### Monitoring

2.16

The monitoring plan for REFINE is based on a formal risk assessment and reviewed and updated as appropriate on at least an annual basis. The REFINE team conduct monitoring checks including consent, eligibility, treatment administration and safety monitoring. Any issues identified will be raised and discussed with the local team. Central monitoring processes have been expanded where possible to replace some of the activities that would normally be completed during on-site monitoring visits in light of the Covid 19 pandemic. On-site monitoring for the REFINE trial will be conducted on a triggered basis (triggers include low data return rate, poor data quality, late reporting on SAEs and critical protocol deviations). Any sites meeting at least 2 of the triggers will be considered for an on-site monitoring visit. The triggers will be reviewed by the trial team at least annually.

### Data management

2.17

Electronic CRFs are used in REFINE. Sites enter data directly into the REFINE Open Clinica Database. Built in validations (value ranges, date inconsistencies, treatment administration) help ensure the data is correct. The REFINE Data Management Plan provides a breakdown of how data is to be acquired, handled, and secured.

### Statistical analysis plan

2.18

For stage I, the primary analysis will consist of a Cox proportional hazards model, where time will be time to progression or censoring, and the main covariate will be binary treatment, defined as standard-of-care (Arm A – standard frequency) or extended frequency (Arm B) ICI. The model will also adjust for the stratification variables. Each cohort will be analysed separately, using a 5% one-sided significance level. All patients will be included and analysed by their schedule allocation (intention to treat – ITT). The hazard ratio for Arm B vs Arm A will then be estimated and will inform the design of stage II, following discussion with relevant oversight committees (Trial Management Group (TMG), Independent Data Monitoring Committee (IDMC) and Trial Steering Committee (TSC)). Strict statistical rules will not be in place, but decisions will be based on the following guidelines:

If the stage I analysis shows that the extended interval arm (2×) is significantly inferior to the standard interval arm (1×), i.e. the confidence interval (CI) for the hazard ratio lies entirely above 1, recruitment will not be continued in the 2× arm, and no arms with further extended intervals (2.5× or 3×) will be opened. The trial committees will discuss whether there is any scientific merit in opening the intermediate interval (1.5×) arm (Fig. 1).If the extended frequency arm is not shown to be significantly inferior, an assessment of non-inferiority will be made. If non-inferiority is shown, (CI for the hazard ratio excludes the non-inferiority margin), then stage II can proceed as planned, opening up arms with further extended intervals (2.5× and 3×). The trial committees will further discuss whether there is merit in adding the intermediate interval (1.5×) arm at this stage.In the event that the stage I results show neither inferiority or noninferiority of the extended frequency arm, (CI for the hazard ratio includes both 1 and the non-inferiority margin), the trial committees will determine which arms will be available in stage II. Safety and quality of life data will be considered alongside the efficacy data, as well as any emerging external evidence, including information from other REFINE cohorts.

Decisions will be made independently for each cohort; not all cohorts may continue to stage II, and different arms may be introduced in each cohort.

Analysis of PFS in stage II will be performed as described for stage I, fitting a Cox model for PFS and estimating hazard ratios comparing extended frequency arms to the standard frequency arm. A 5% (one-sided) significance level will be used throughout. Analysis will begin by assessing the most extended frequency arm. If that arm demonstrates non-inferiority, no further arms will be compared, and all arms will be considered for the phase III expansion of REFINE. If non-inferiority is not demonstrated, the next most extended frequency arm is assessed in the same manner, and so on until either an arm demonstrates non-inferiority, or all arms have been assessed.

If there is evidence of non-proportional hazards, or if other characteristics of the data suggest a likely gain in power, restricted mean survival (RMST) with a t-star of nine months will be used to analyse these data instead [24].

For time to event analyses, patients without an observed event will be censored at the date of their last assessment. It is anticipated that the majority of censoring will be administrative censoring at the time of analysis, therefore the assumption of non-informative censoring should be valid. Patterns of censoring will be assessed and if necessary, for example if a high proportion of patients are lost to follow-up, sensitivity analyses may be performed to assess the robustness of results.

Analysis of categorical variables will compare arms using the chi-squared or Mann-Whitney test, with analysis of continuous variables using a *t*-test. Continuous secondary outcome measures such as QOL may utilise linear mixed models to obtain an estimate for the mean difference between treatment arms. Models will include a random intercept, plus arm, time-by-arm interaction and randomisation stratification variables as fixed effects. Model assumptions will be examined using residual analysis and examination of graphical displays such as normal quantile plots. For quality-of-life analyses, initial analyses will use a complete case approach, without imputation of any missing data. Levels and patterns of missing data will be assessed, and if necessary, sensitivity analyses will be conducted using multiple imputation techniques.

All estimates will be presented along with their 95% confidence interval. Additionally, to assess non-inferiority, PFS hazard ratios will also include a 90% confidence interval, corresponding to the 5% one-sided significance interval. All disease cohorts are designed to be independently powered and analysed.

All analyses will be conducted using the intention-to-treat (ITT) population, including all randomised patients. The primary outcome measure of PFS will also be assessed using the per-protocol (PP) population, which will exclude any ineligible patients, and any patients who do not receive any treatment after randomisation.

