## Introduction

1

Immune checkpoint inhibitors (ICI) have revolutionised cancer treatment over the last decade, resulting in durable responses and long-term survival in several cancer types [1–3]. ICI are monoclonal antibodies that target immune checkpoints including programmed cell death 1 receptor (PD-1) and its ligand 1 (PD-L1), which play a key role in maintaining immune homeostasis. Inhibition of these checkpoints restores the ability of the immune system to recognise and destroy cancer cells.

Despite their success, ICI impose a significant burden on patients and healthcare systems. ICI are routinely administered on a continuous schedule of frequent intravenous administrations (currently every 2–6 weeks) until cancer progression or the development of unacceptable toxicity. This approach requires a major commitment of resources for individual patients and health services alike. Disappointingly, due to the financial burden associated with treatment, ICI are not available globally to many who might benefit [4].

At present, there is limited understanding around predictive biomarkers for initial use or continued treatment with ICI, resulting in significant over treatment [5,6]. This increases treatment toxicity, negatively impacts quality of life (QOL) and has a significant and potentially avoidable financial impact on healthcare services.

Physiological efficacy of ICI (measured by PD-1 T cell receptor occupancy) is observed at much lower doses than those that have become standard of care (SOC) [7] and pharmacodynamic studies indicate sustained target occupancy on T cells of >70% for at least 2 months despite a pharmacological half-life of 2–3 weeks [8]. Furthermore, it has been observed that the rate of clearance of ICI decreases in patients responding to treatment as their disease status improves [9]. The potential prolonged physiological activity of these drugs means that as an alternative to early cessation, extending the interval of administration (i. e. reducing the frequency) should be possible, without compromising outcomes. This is supported by simulation analyses for pembrolizumab and nivolumab [10].

A number of clinical trials are currently testing early cessation in patients experiencing clinical response, either at a pre-determined timepoint such as 1 year (DANTE in melanoma or SAVE in non-small cell lung cancer [11,12]) or at maximal clinical response (SAFE-STOP and PET-STOP, in melanoma [13,14]).

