### Outcome measures

2.2

The primary outcome measure in REFINE is progression free survival (PFS). PFS is defined as the interval from randomisation to first evidence of local recurrence, new primary cancer, distant metastases (new or progression), or death from any cause, whichever occurs first. Analysis will be performed approximately 6 months after stage I recruitment has completed and will inform the design of the second stage.

The following secondary outcome measures will be analysed:

Overall survival (OS)Quality of Life (QoL) (EORTC QLQ-C30 and EQ-5D-5L)Treatment-related toxicityMean incremental cost per patientMean incremental QALYs per patient (calculated from EQ-5D-5L)Cost-utility analysis assessing cost-effectiveness of reduced versus standard frequency administrationFeasibility of recruitment to each cohort

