### Sample size

2.3

REFINE will enrol 160 patients into stage I for each cohort (80 patients randomised to each arm). This will provide 80% power at a 5% one-sided significance level to detect an absolute reduction of 20 percentage points in 9-month PFS. This number of patients would also be sufficient to demonstrate non-inferiority of the extended frequency arm, using a hazard ratio non-inferiority margin of 1.94 for the renal cohort (and e.g. 1.85 for the melanoma cohort) which should correspond to a 20-percentage points NI margin on the 9-month PFS difference scale. 9-month PFS rates are estimated to be 70% in the renal cohort [1,18]. For all cohorts, stage I analysis will be performed when approximately 30 PFS events have been observed in the control arm, which is expected to occur around six months after the completion of recruitment.

Following analysis of stage I data, assuming satisfactory outcomes in patients treated with the extended dosing interval, stage II will then test multiple experimental arms with the maximal interval being 3 times the SOC. The second stage intends to enrol up to an additional 200 patients per cohort dependent on stage I results. Under the same assumptions made for the stage 1 sample size calculations, this will provide around 80% power to demonstrate non-inferiority for the extended interval arm, relative to SOC using the same non-inferiority margins.

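### The primary non-inferiority test may be switched to nine-month RMST because the data suggest more power, while the stated margins and decision guidelines are all on the hazard ratio

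*Protocol article*

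**What the plan says.** Section 2.2 (Outcome measures) names PFS as the primary outcome. Section 2.3 (Sample size) plans 80 patients per arm in each cohort, for "80% power at a 5% one-sided significance level to detect an absolute reduction of 20 percentage points in 9-month PFS". Non-inferiority is set "using a hazard ratio non-inferiority margin of 1.94 for the renal cohort (and e.g. 1.85 for the melanoma cohort"). The article equates these margins with a loss of 20 points in PFS at nine months.

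Section 2.18 makes a Cox model, adjusted for the stratification variables, the primary analysis. Its guidelines for stage II are worded on the hazard ratio: inferiority if the interval lies above 1, and non-inferiority if the "CI for the hazard ratio excludes the non-inferiority margin". The 90% interval used to judge non-inferiority is likewise specified for PFS hazard ratios.

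After describing the stage II testing sequence, the section says that Cox will give way to another method in either of two situations. One is evidence of non-proportional hazards. The other is "if other characteristics of the data suggest a likely gain in power, restricted mean survival (RMST) with a t-star of nine months" as the replacement. The article gives no threshold for either situation and does not say whether the data characteristics are pooled or compared by arm.

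**The concern.** A confirmatory non-inferiority test should be fixed before outcome data are seen. Here one stated reason for changing it is that the alternative looks likelier to succeed. That is a choice of test by expected result, and it gives two routes to a pass where the error rate was set for one.

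The switch also changes what is being compared. The hazard ratio uses all follow-up to the analysis. RMST to nine months measures area under the curve up to that point and gives little weight to events close to it. If extended dosing loses efficacy late, the nine-month PFS difference can reach the protocol's 20-point limit while the RMST loss stays small. Some lag is plausible on the article's own account, since the Introduction cites "sustained target occupancy on T cells of >70% for at least 2 months". Late separation is itself non-proportional hazards, so it can also set off the first trigger.

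At stake is the evidence on which the 2.5× and 3× arms are considered after stage I, and on which arms are put forward for phase III after stage II.

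**Working it through.** **Inputs from the article.** 80 per arm; control 9-month PFS 70% (renal); margin 20 points or HR 1.94; one-sided 5% (section 2.3). About 12 months' accrual plus about 6 months (section 2.15), so follow-up of 6 to 18 months. Scans every 12 weeks (section 2.9).

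**Assumptions.** Exponential control PFS, uniform accrual, the RMST margin in step 2, and the separation times in steps 4 and 5.

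**1. The plan's own figures reproduce.** HR margin = ln(0.50)/ln(0.70) = 1.943. Expected control events = 29.8 of 80, against about 30 stated. With 2 × 29.8 = 59.6 events, Schoenfeld power at HR 1.94 is 82%.

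**2. The margin translated to RMST.** RMST(9) = (1 − S(9))/λ.
- Control: λ = −ln(0.70)/9 = 0.03963; RMST = 0.30/0.03963 = 7.57 months.
- At the margin: λ = −ln(0.50)/9 = 0.07702; RMST = 0.50/0.07702 = 6.49 months.
- Implied margin: 7.57 − 6.49 = 1.08 months.

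The value depends on the model. If progression is seen only at the 12-weekly scans, the same two hazards give step curves that differ by 0.79 months.

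**3. Error at the margin under proportional hazards (simulated).** Cox about 5%, RMST about 5%. Switching on a proportional-hazards test gives 5.9%. Taking whichever test passes gives about 7 to 8%, an upper figure. With truly equal arms, power is about 82% for Cox and 84 to 85% for RMST.

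**4. Late separation, with the extended arm at 50% at nine months (20 points worse).** Hazards are equal to time τ, then constant and higher. For τ = 2.76 months (12 weeks):
- S(τ) = 0.70^(2.76/9) = 0.8964.
- Late hazard = ln(0.8964/0.50)/6.24 = 0.0936, a late HR of 2.36.
- RMST loss = (0.8964 − 0.70)/0.03963 − (0.8964 − 0.50)/0.0936 = 0.72 months, inside 1.08.

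| Separation | Late HR | True RMST(9) loss | RMST passes | Cox passes |
|---|---|---|---|---|
| 2.76 months | 2.36 | 0.72 | about 21% | about 5% |
| 4.5 months | 2.89 | 0.51 | about 40% | about 4% |
| 6 months | 3.83 | 0.33 | about 57% | about 3% |

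Pass rates come from several thousand simulated trials per row. If RMST is used only after a positive proportional-hazards test, the pass rates are 31% at 4.5 months and 48% at 6 months.

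Scan timing works the same way. A 20-point drop first seen at week 36 (8.29 months) costs 0.20 × (9 − 8.29) = 0.14 months of RMST(9).

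**5. Early harm, same margin.**
- HR 2.8 to 6 months, then 0.4 (9-month PFS 70% vs 49%): Cox passes about 8 to 10%, RMST under 1%.
- HR 3 to 4.5 months, then 0.9 (70% vs 50%): Cox about 7%, RMST 0.2%.

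Here the switch protects.

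**6. How far the horizon could move in stage I.** Expected control patients at risk = 80 × 0.70^(t/9) × (18 − t)/12.
- 9 months: 80 × 0.700 × 0.75 = 42.
- 12 months: 80 × 0.622 × 0.50 = 25.
- 15 months: 80 × 0.552 × 0.25 = 11.
- 18 months: 0.

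**The case against.** RMST is a recognised response to non-proportional hazards, and nine months is the trial's own horizon: the 20-point margin is set there, and the analysis is timed so that most patients have at least nine months on trial. That stands. The objection is to choosing the test from the data for its power and to the mismatch with the stated decision scale, not to RMST itself.

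A reader might infer that no RMST margin exists. The article does not support that: it condenses a fuller protocol, and a margin or a switching threshold may be given there or in the analysis plan. All that can be said is that the margins and guidelines shown are on the hazard ratio.

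A reader might also infer that the switch always favours a pass. Step 5 shows the opposite under early harm. The separation times in step 4 are assumptions too. Receptor occupancy of at least two months makes some lag plausible but does not establish 4.5 or 6 months.

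The article does not say to run both tests and keep the better one, so 7 to 8% is a ceiling. If the data characteristics were pooled and blinded, inflation could be smaller.

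Finally, section 2.18 says strict rules will not apply at stage I, several committees discuss the result, and stage II needs a regulatory amendment. No single test opens the 2.5× and 3× arms automatically. The stage II sequence carries no such softening, and the switching sentence follows it.

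**Conclusion.** The point holds in limited form and should be fixed; it does not invalidate the design. The power trigger is stated outright and is not a detail left to another document. Its effect on the error rate is modest: from 5% to about 6% with a proportional-hazards pre-test, and at most about 7 to 8%.

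The larger issue is the change of estimand. Under late separation, nine-month RMST would pass an arm 20 points worse in roughly 21% (separation at 2.76 months) to 57% (6 months) of trials, against about 3 to 5% for Cox. Those figures rest on exponential control PFS, an assumed 1.08-month margin and assumed separation times. Under proportional hazards the two tests agree closely, and under early harm Cox is the more lenient. The conclusion is therefore that the choice of test should not depend on the data, not that RMST is biased towards non-inferiority.

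**What to change.** In section 2.18:
- Delete the clause that allows a switch for a likely gain in power.
- Keep the Cox hazard ratio against its stated margin as the primary non-inferiority test in both stages.
- Report RMST as supportive, against a margin fixed in advance from the 20-point margin (renal: about 1.08 months at nine months under exponential PFS), and state the model used for the conversion.
- If hazards are non-proportional, also report the 9-month PFS difference with its 90% interval against 20 points. This covers early harm, where Cox alone is lenient.
- Add RMST at a later horizon only where enough patients remain at risk: about 12 to 15 months in stage I. Eighteen months is not workable, because almost nobody is at risk then.

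The cost is one reworded paragraph, a little extra analysis, and about 2 to 3 points of possible power under equal hazards. If the full protocol or analysis plan already fixes a switching rule and an RMST margin, the article's wording should be brought into line with it.

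### Toxicity and other categorical outcomes are assigned unadjusted tests, and adjustment of continuous secondary outcomes is only optional, although allocation is minimised on factors that the primary model adjusts for

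*Protocol article*

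**What the plan says.** Four statements in the protocol article bear on this.

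- **Allocation (section 2.7).** Patients are randomised "using minimisation (with a random element) with stratification by a small number of important stratification factors". The article does not name the factors. Stage I allocation is 1:1.
- **Primary analysis (section 2.18).** The Cox model for PFS adjusts for the stratification variables.
- **Simple tests (section 2.18).** "Analysis of categorical variables will compare arms using the chi-squared or Mann-Whitney test", and continuous variables are compared with a t-test. None of these tests takes covariates.
- **Mixed model (section 2.18, same paragraph).** Continuous secondary outcomes such as quality of life may be analysed with linear mixed models. When used, these contain the randomisation stratification variables as fixed effects.

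Of the secondary outcomes in section 2.2, treatment-related toxicity is the one that plainly falls to the categorical tests. No adjusted method is offered for it. Section 2.18 also promises a 95% confidence interval with every estimate.

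**The concern.** Minimisation makes the arms more alike on the chosen factors than simple randomisation would. If those factors predict the outcome, the difference between arms varies less from one possible allocation to another. A t-test or chi-squared test does not use this. It leaves the variation due to the factors in its standard error, so the standard error is too large, p-values are too large and power is lower than the design could give. Adjusting for the factors brings the analysis back into line with the allocation, as the primary model already does.

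A conservative comparison can hide a difference in either direction. Less toxicity is part of the rationale for the extended interval, and more toxicity would be a reason for caution. When the stage I PFS result is inconclusive, section 2.18 has the committees consider safety and quality of life alongside efficacy.

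**Working it through.** **The plan's own figures.** The article gives no power or effect size for any secondary outcome, so only the primary calculation can be reproduced.

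- Section 2.3 says: "This will provide 80% power at a 5% one-sided significance level to detect an absolute reduction of 20 percentage points in 9-month PFS". The renal control rate is 70%, so the comparison is 70% v 50% with 80 per arm. A two-proportion calculation gives 83.1% power without continuity correction and 78.6% with it, consistent with the stated 80%.
- The margin is ln(0.5)/ln(0.7) = 1.943, matching 1.94.
- Section 2.3 also says "stage I analysis will be performed when approximately 30 PFS events have been observed in the control arm", so about 60 events in total if the hazard ratio is 1. Freedman's formula needs 61 events for 80% power, and 60 events give 79.7%.

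The primary sample size is therefore coherent, and nothing below changes it.

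**Inputs for the secondary comparisons.** 80 per arm (section 2.3) and a two-sided 5% test. The share of outcome variance explained by the minimisation factors, R², is not in the documents; it is assumed to lie between 0 and 0.3.

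**Size of the unadjusted t-test.** With arms balanced on the factors, the true standard error of the difference is s = √(1 − R²) times the one the test uses. The true two-sided size is therefore 2 × [1 − Φ(1.96/s)].

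**Power.** Take the effect that has 80% power when R² = 0: (1.96 + 0.842) × √(2/80) = 0.443 SD.

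- Unadjusted power = Φ(0.842/s)
- Adjusted power = Φ(2.802/s − 1.96)

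| R² | 1.96/s | True size, unadjusted | Power, unadjusted | Power, adjusted | Points forgone |
|---|---|---|---|---|---|
| 0 | 1.96 | 5.0% | 80.0% | 80.0% | 0 |
| 0.05 | 2.01 | 4.4% | 80.6% | 82.0% | 1.4 |
| 0.1 | 2.07 | 3.9% | 81.3% | 84.0% | 2.7 |
| 0.2 | 2.19 | 2.8% | 82.7% | 87.9% | 5.2 |
| 0.3 | 2.34 | 1.9% | 84.3% | 91.8% | 7.5 |

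For a one-sided 5% test the true sizes at R² of 0.1, 0.2 and 0.3 are 4.2%, 3.3% and 2.5%.

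**Check by simulation.** The formula assumes perfect balance, whereas the trial's minimisation has a random element. A simulation used 160 patients, three binary factors, an assumed probability of 0.8 of the preferred arm and 4,000 trials per setting. The Monte Carlo error of a 5% rate is √(0.05 × 0.95/4000), about 0.3 points.

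| R² | t-test size | Adjusted linear model size | Power, t-test | Power, adjusted | Chi-squared size, binary outcome |
|---|---|---|---|---|---|
| 0 | 4.8% | 4.9% | 79.5% | 79.4% | 4.5% |
| 0.1 | 3.9% | 5.1% | 80.6% | 83.6% | 4.5% |
| 0.2 | 2.7% | 4.8% | 81.6% | 88.1% | 3.3% |
| 0.3 | 1.9% | 5.0% | 83.6% | 91.4% | 3.8% |

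The continuous results agree with the formula. For the binary outcome R² refers to the underlying continuous scale. There is no change at 0.1 and a small, uneven reduction above it. No adjusted binary model was simulated, so the power forgone for toxicity is not quantified here.

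**The case against.** **A reader might infer that all secondary outcomes are analysed without adjustment.** The article does not support that. The sentence speaks of categorical and continuous variables and does not claim to govern every secondary outcome. Overall survival is a time-to-event outcome. Costs and QALYs have their own methods in section 2.4, with bootstrapping. Feasibility of recruitment is not a comparison of arms. For quality of life, the mixed model in the same paragraph already has the adjustment, although it is optional.

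**The size rests on something unseen.** This stands. The factors are called important but not named, and nothing shows that they predict toxicity. If R² is near zero, the effect disappears. The larger figures are for continuous outcomes, while the outcome most clearly caught by the sentence is categorical, where the effect is smaller.

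**The lost power is relative.** This also stands. In the table, unadjusted power does not fall below its value at R² = 0, and no secondary outcome has a power target to miss.

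**A reader might infer that a toxicity p-value steers stage II.** Section 2.18 mentions safety and quality of life only for the inconclusive result, together with efficacy and external evidence, and says that no strict statistical rules apply.

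**Conservative tests in a phase II trial are acceptable, and covariate detail belongs in the analysis plan.** The tests are not invalid in the sense of excess false positives. But the article does not leave the matter open: it names the tests, and they do not match the allocation or the primary model.

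**Conclusion.** The point holds as a minor improvement of limited scope. The named tests for categorical variables, in practice treatment-related toxicity, and the t-test for any continuous outcome not given the mixed model ignore the factors on which allocation is minimised. Where those factors are prognostic, the tests are conservative. For continuous outcomes, over an assumed R² of 0 to 0.3, the true size of a nominal two-sided 5% t-test runs from 5% to about 1.9%, and 0 to about 8 points of power are given up against an adjusted analysis. At R² of 0.1 or below the loss is at most about 3 points. For binary outcomes it is smaller and may be negligible.

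These figures assume 80 per arm, near balance on the factors and a linear effect of the factors on the outcome. They do not show that any planned comparison would give a misleading result. The primary PFS analysis and the sample size are untouched.

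**What to change.** In section 2.18, and in the analysis plan:

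- **Continuous secondary outcomes:** change *may* to *will* for the mixed model with the stratification variables. Where an outcome is measured only once, use linear regression adjusted for those factors, with the baseline value as a covariate where it is collected.
- **Categorical outcomes such as worst toxicity grade:** make logistic or proportional-odds regression adjusted for the stratification factors the main comparison, reported with a 95% confidence interval. This also supplies the estimate and interval that the section promises, which a chi-squared or Mann-Whitney test does not itself give.
- **Sparse events:** keep the unadjusted test or an exact test where there are too few events to fit the model, and state in advance when this applies.

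The cost is a change of wording, since the factors are recorded at randomisation and are already in the primary model. There is a small downside: the adjusted odds ratio is conditional on the factors, so it is not the same quantity as the crude one, and it can be unstable with few events.
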